### Inclusion and exclusion criteria

Screening for inclusion and exclusion criteria is carried out by qualified research workers in close contact with clinical staff.

#### Inclusion criteria

• Adult age (18-60 years) at intake;

• Mental disorder of any kind as main diagnosis established by case notes or staff communication using SCID criteria;

• Presence of severe mental illness (Threshold Assessment Grid ≥ 5 points and illness duration ≥ 2 years);

• Expected contact with mental health services (excluding inpatient services) during the time of study participation;

• Sufficient command of the host country's language;

• Capable of giving informed consent.

#### Exclusion criteria

• Main diagnosis of mental retardation, dementia, substance use or organic brain disorder;

• Cognitive impairment severe enough to make it impossible to give meaningful information on study instruments;

• Treatment by forensic psychiatric services.

### Instruments and data collection

Using intensive literature search and focus group methodology [39], three instruments were developed in the course of preparing the start of the study (April - October 2009):

(1) *Clinical Decision Making Style Scale *(CDMS CEDAR) in order to comprehensively assess nature (preferences, autonomy, information seeking) and stability of patients' and clinicians' decision making style both at baseline and at one-year follow-up (21 items);

(2) *Clinical Decision Making in Routine Care Scale *(CDRC CEDAR) in order to measure key aspects of CDM from the patient and clinician perspectives as they unfold in routine care (4 items plus 3 follow-up items measuring degree of implementation of the decision identified at the last *CEDAR *assessment and significant life events since then).

(3) *Clinical Decision Making Involvement and Satisfaction Scale *(CDIS CEDAR) in order to assess subjective satisfaction and involvement with clinical decision making (7 items).

Table 3 lists the instruments used in *CEDAR *to assess relevant variables by time points of their application and rater perspective(s).

**Table 3 T3:** Study instruments by perspective and measurement point.

*Variable*	*Instrument*	*Perspec-tive*	*Measurement point*		
			
			t0	t1-t5	t6
Clinical characteristics (diagnosis, illness duration)	Structured Clinical Interview for DSM-IV on the basis of case notes (SCID [45,46])	P^R^	✓		

Sociodemographic status, service use	Client Sociodemographic and Service Receipt Inventory (CSSRI-EU [49])	P^R^	✓		✓

Illness severity	Threshold Assessment Grid (TAG [47])	P^R^	✓		✓

CDM Style	Clinical Decision Making Style Scale (CDMS CEDAR)	P/S	✓		✓

CDM in Routine Care	Clinical Decision Making in Routine Care Scale (CDRC CEDAR)	P/S	✓	✓	✓

CDM Involvement and Satisfaction	Clinical Decision Making Involvement and Satisfaction Scale (CDIS CEDAR)	P/S	✓	✓	✓

Needs	Camberwell Assessment of Need Short Appraisal Schedule (CANSAS [48,49])	P	✓	✓	✓

Quality of Life	Manchester Short Assessment of Quality of Life (MANSA[50])	P	✓		✓

Therapeutic relationship	Helping Alliance Scale (HAS [51])	P/S	✓	✓	✓

Symptomatic impairment	Outcome Questionnaire (OQ-45.2 [52])	P	✓		✓
	Health of the Nation Outcome Scale (HoNOS [53])	S	✓		✓

Functioning	Global Assessment of Functioning Scale (GAF [54])	S	✓		✓

Recovery	Stages of Recovery Instrument (STORI-30 [55])	P	✓		✓

*Notes*. CDM: Clinical Decision Making; P: Patient; S: Staff; P/S: Patient and Staff; P^R^: Patient, researcher-led, t0: baseline assessment; t1-t5: intermediate assessments (2, 4, 6, 8, and 10 months); t6: final assessment (12 months).

Unit of analysis for the CDM measures is always the decision arrived at during the meeting prior to the current assessment point as indicated by the patient. Furthermore, adherence to the decision indicated at the previous time point is scrutinized via the respective items in the CDRC follow-up ("Have you implemented the decision identified in your last *CEDAR *assessment two months ago?").

All instruments used were made available in all centres' languages via intensive forward and backward translation following common standards [40]. Data is collected via questionnaires (filled in by the patient or his or her key worker) or via interviews conducted by the *CEDAR *study worker. Data entry modes are via computer or paper-pencil forms.

### Sample size

Sample size calculation was performed for the analyses of the primary outcome, i.e. whether needs rated via the CANSAS-P are affected by the quality of decision making during the one-year observation time. Following Hedeker et al. [56], assuming a constant group effect over time with a random-effect structure and auto-correlated residuals, and estimating a panel attrition of 5% at each measurement point, a small effect size (0.2 SD) should be detected with a power of 0.80 at a two-tailed significance level of 0.05 with a group sample size of N = 222 for six time points (and of N = 238 for eight time points). Required sample size for seven time points as in our design was estimated via interpolating the difference in N from six to eight time points with all other elements of the equation remaining unchanged: N = (222 + 238)/2 = 230. For this analyses, participants will be grouped in two categories of quality of decision making, resulting in a total required group size at T0 of N = 460. This means that baseline sample size to be recruited at each centre is N = 77 (after rounding to the next higher integer).

Variation between centres will be taken into account by treating centres as clusters. According to Donner [57], the variance inflation factor (or design effect) is given by *IF *= 1 + (*m *- 1) * *ρ*; where *m *= cluster size, and *ρ *= ICC (inter-cluster correlation).

With m = 77 and ρ = .003, IF = 1,22, resulting in an adjusted sample size of N = 561 (94 per centre).

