**Methods/Design:**

The study entitled "Clinical decision making and outcome in routine care for people with severe mental illness" (CEDAR) is carried out in six European countries (Denmark, Germany, Hungary, Italy, Switzerland and UK). First, CEDAR establishes a methodology to assess CDM in people with severe mental illness. Specific instruments are developed (and psychometric properties established) to measure CDM style, key elements of CDM in routine care, as well as CDM involvement and satisfaction from patient and therapist perspectives. Second, these instruments are being put to use in a multi-national prospective observational study (bimonthly assessments during a one-year observation period; N = 560). This study investigates the immediate, short- and long-term effect of CDM on crucial dimensions of clinical outcome (symptom level, quality of life, needs) by taking into account significant variables moderating the relationship between CDM and outcome.

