### Design and recruitment

*CEDAR *is a naturalistic prospective longitudinal observational study with bimonthly assessments during a 12-month observation period (T0-T6). Participants are being recruited from caseloads of outpatient/community mental health services at six centres throughout Europe: Department of Psychiatry II, Ulm University, Germany (coordinating centre); Section of Recovery at Institute of Psychiatry, London, U.K.; the Department of Psychiatry at Second University of Naples, Italy; the Department of Psychiatry at Debrecen University, Hungary; the Unit for Psychiatric Research at Aalborg Psychiatric Hospital, Denmark; and the Department of General and Social Psychiatry at University of Zurich, Switzerland.

Before the start of recruitment in November 2009, the study protocol has been approved by all centres' ethics committees. Only subjects will be included who provided valid informed consent. Each potential participant in this research project, prior to consent, will be clearly informed of its goals, its possible adverse events and the possibility to refuse to participate or to withdraw consent without any adverse consequences. Informed consent will be asked only of persons able to freely understand and question.

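### The centre design effect is misprinted (1.228, not 1.22) and taken at 77 instead of the 94 per centre to be recruited; by the plan's own formula, power at 561 to 564 patients is about 0.78, not 0.80

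*Protocol article*

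**What the plan says.** The Sample size section sizes the study for the primary outcome, needs rated on the CANSAS-P. It claims that "a small effect size (0.2 SD) should be detected" "with a power of 0.80 at a two-tailed significance level of 0.05". Attrition is already in the base figure, since the calculation is described as "estimating a panel attrition of 5% at each measurement point". Interpolation between two published group sizes gives 230 per group, "resulting in a total required group size at T0 of N = 460", or 77 per centre after rounding up.

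Centres are then treated as clusters. The inflation factor is 1 + (m − 1)ρ, "where *m *= cluster size". The result is stated as "With m = 77 and ρ = .003, IF = 1,22, resulting in an adjusted sample size of N = 561 (94 per centre"). Design and recruitment fixes the number of clusters: patients come from "outpatient/community mental health services at six centres throughout Europe".

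**The concern.** The sentence that takes 77 as the cluster size ends by recruiting 94 per cluster. In a design that can add clusters, inflating the total leaves the cluster size unchanged, and one application of the formula is enough. Here there are six centres and no more, so every added patient makes a centre larger and raises the design effect again. A factor evaluated at the centre size before inflation is therefore too small for the study that will be run. The printed factor is also not what the formula returns at the printed inputs.

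This paragraph is the article's only justification of the study's size. A reader who applies its formula to its own inputs obtains neither the stated total nor the stated power.

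**Working it through.** **Inputs, all from the protocol article.** Base total 460 for power 0.80 at two-sided 0.05; six centres; ρ = .003; IF = 1 + (m − 1)ρ; m = 77 before inflation and 94 after.

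**1. The plan's figure.** 460 × 1.22 = 561.2, which is the stated 561; 561/6 = 93.5, which rounds up to 94 per centre. The stated total therefore reproduces, but only with the factor 1.22.

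**2. The factor at the printed inputs.** 1 + 76 × .003 = 1.228. Then 460 × 1.228 = 564.9, so 565 patients (95 per centre). This exceeds both 561 and 6 × 94 = 564, but only just: the difference from 561 is 4 patients, or 0.7%. If this were the only error, power at 561 would be 0.797.

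**3. The factor at the recruited centre size.** 1 + 93 × .003 = 1.279. One step gives 460 × 1.279 = 588.3.

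**4. The self-consistent total.** With six centres m = N/6, so

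N = 460 × [1 + (N/6 − 1) × .003]

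N × (1 − 460 × .003/6) = 460 × .997

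N = 458.62/0.77 = 595.6, or 596 (about 99 to 100 per centre).

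This is 35 patients, or 6.2%, above 561.

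**5. Power at the planned size.** Scale so that an effective total of 460 has power 0.80:

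power = Φ[(1.960 + 0.842) × √(N_eff/460) − 1.960], where N_eff = N/IF and IF is taken at m = N/6.

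| N | IF | N_eff | Power |
|---|---|---|---|
| 561 | 1.2775 | 439 | 0.782 |
| 564 | 1.279 | 441 | 0.783 |
| 596 | 1.295 | 460 | 0.800 |

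**6. Allowing for attrition in the centre size.** Read the plan's 5% loss per measurement point as a fraction 0.95^k remaining at wave k. The mean over the seven waves (k = 0 to 6) is 0.862, so a centre of 94 averages 94 × 0.862 = 81. Then IF = 1 + 80 × .003 = 1.240. Power is 0.794 at 561 and 0.796 at 564, and the self-consistent total is about 572, 2% above 561. Putting an average size into the formula is an approximation.

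**The case against.** The strongest defence is that nothing of practical weight is wrong. Five arguments support it.

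- **The gap is under 2 points of power.** The base figure is itself an interpolation between 222 and 238, so an error of this size is comparable to approximations already accepted. This stands as to size. It does not make the printed factor or the power statement correct.
- **The factor 1.22 may come from an unrounded ρ.** With ρ = .0029, 1 + 76 × .0029 = 1.2204 and 460 × 1.2204 = 561.4. This is possible, so deliberate truncation is not shown. It explains only the smaller discrepancy: at m = 94 the factor would still be 1 + 93 × .0029 = 1.270.
- **Attrition makes the observed centres smaller than 94.** This stands and removes more than half of the gap, leaving power at about 0.79.
- **The formula suits a factor that is constant within a cluster.** Decision-making quality is measured on patients and their clinicians and can differ between patients in the same centre, so the inflation is probably too severe for this comparison. This also stands. With no inflation, 564 patients split into equal groups would have power of about 0.87. That figure needs both quality groups to be balanced within centres. The article does not say this, and it leaves the groups to be found by cluster analysis, so 0.87 cannot replace the stated power.
- **The totals 560, 561 and 564 are rounding.** Agreed: the abstract's "bimonthly assessments during a one-year observation period; N = 560" is a rounded 561, and 564 is 6 × 94. This is no contradiction.

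A reader might infer that the study is materially underpowered and must recruit 596. The documents do not support that: 596 is what this formula returns, the loss at the planned size is about 2 points, and the formula probably overstates the loss. A reader might also object that ρ = .003 is given without a source. In a condensed article whose full protocol is not shown, that is not an error, and the point here takes ρ as stated.

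**Conclusion.** The point holds as an arithmetic correction. The stated factor of 1.22 should be 1.228 at m = 77, and 1.279 at the 94 per centre to be recruited. Almost all of the effect comes from the choice of m; the misprinted factor alone is immaterial. By the plan's formula, the consistent total is about 596 against 561 stated, and 561 to 564 patients give power of about 0.78, or about 0.79 with attrition in the centre size.

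This rests on the plan's own assumptions: ρ = .003, six centres of equal size, two equal groups, and a base of 460 taken as giving exactly 0.80. The shortfall is small, its direction is unfavourable under the stated formula, and the true loss is probably smaller still. It is worth correcting because the stated total and power do not follow from the inputs beside them, not because the study's feasibility is in doubt.

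**What to change.** Leave enrolment as planned. In the Sample size section, replace the factor 1.22 at m = 77 with 1.279 at m = 94, and state that 94 per centre gives power of about 0.78 under ρ = .003. One sentence may add that the figure rises to about 0.79 when attrition is allowed for in the observed centre size, and that the inflation is probably conservative because quality of decision making can vary within centres. The cost is one reworded paragraph and a slightly less favourable power figure; recruitment, assessments and analysis do not change.

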### Procedures

Descriptive reports include absolute and relative frequencies for categorical variables, and means and standard deviations (and minimum, median and maximum as well the 25%- and 75%-percentiles where applicable) for continuous variables. Between-centre differences will be exploratively tested by χ^2^-Tests for factors and by T-tests or ANOVAs resp. for continuous variables. The effect of the intervention on needs, quality of life and symptomatic impairment will be tested by means of hierarchical linear models [41] with the time variable t (0, 2, 4, 6, 8, 10 and 12 months). Random effects will be observations "within" subject over time, and fixed effects will effects of time, quality of clinical decision making and other covariates (see Figure 2) on the given outcome measure. All available data will be used in the data analysis. Sum scales will be prorated in case of missing values on less than 80% of the single items making up the score. Furthermore, cluster analyses will be used to arrive at meaningful categories of quality of decision making from the CDM measures applied, and chain modelling [42] will be used to draw possible causal inferences from the panel data.

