### Develop and validate methodology to measure the quality of clinical decisions

Instruments to capture structure, process, and outcome of decision making in the care of people with SMI will be developed and empirically validated: (a) Structure: Clinical decision making style and key elements of clinical decisions; (b) Process: Contribution of patient and clinician to CDM, patient behaviour (immediate and long-term); (c) Outcome: Satisfaction with CDM, and clinical outcome (immediate and long-term). Since there is no current gold standard for a clinical decision, *CEDAR *will contribute to an outcome-oriented conceptualisation of CDM quality: Clinical decisions of a "good quality" are those with a strong association with good clinical outcome.

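### As worded, the proration rule sets its 80% limit on missing items, so a sum score may rest on just over 20% of its items

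*Protocol article*

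**What the plan says.** The Procedures section gives one rule for incomplete questionnaires: "Sum scales will be prorated in case of missing values on less than 80% of the single items making up the score". Just before it stands "All available data will be used in the data analysis". No other section sets a stricter minimum or a rule for a particular instrument.

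Instruments and data collection gives the lengths of the three new scales:
- CDIS: "subjective satisfaction and involvement with clinical decision making (7 items")
- CDMS: "decision making style both at baseline and at one-year follow-up (21 items")
- CDRC: "4 items plus 3 follow-up items measuring degree of implementation of the decision"

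These scales supply the exposure. In Procedures, "cluster analyses will be used to arrive at meaningful categories of quality of decision making from the CDM measures applied", and quality of decision making then enters the hierarchical linear models as a fixed effect. The Discussion subsection on developing and validating the methodology also lists satisfaction with decision making as an outcome: "c) Outcome: Satisfaction with CDM, and clinical outcome (immediate and long-term").

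**The concern.** Proration replaces each missing item by the mean of the answered ones. That is reasonable when a few items are missing. When most are missing, the score is largely imputed but carries the same weight as a complete one. The sentence as worded permits this for every sum scale in the study.

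Two places are exposed:
- **The exposure.** The decision-making scales are clustered into quality categories, and the primary analysis compares needs (CANSAS-P) between two such categories. Extra error in the scores can misclassify participants, which would typically weaken an association. The Sample size section plans for an effect of only 0.2 SD and makes no allowance for such error.
- **The outcomes.** Needs, quality of life and symptom scores follow the same rule and would lose precision, to a degree that depends on scale length.

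An analyst who programs the sentence literally admits mostly imputed scores. One who guesses a different intention departs from the published plan.

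**Working it through.** The 80% limit is a stated rule, not a derived figure, so there is no calculation in the plan to reproduce. The check is what the rule permits.

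**Step 1: inputs.** CDRC 4 items, CDIS 7 and CDMS 21 come from Instruments and data collection. Each is treated here as one sum score. The article gives no length for the outcome scales. I assume 45 items for OQ-45.2 (from its name) and a range of 20 to 25 for CANSAS.

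**Step 2: formula.** For a scale of k items, the rule as written allows the largest m (items missing) with m/k < 0.80. A rule of at least 80% answered allows the largest m with m/k ≤ 0.20. Items left = k − m.

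| Scale | k | As written: most missing | Items left | At least 80% answered: most missing | Items needed |
|---|---|---|---|---|---|
| CDRC (if summed) | 4 | 3 (3/4 = 75%) | 1 | 0 | 4 |
| CDIS | 7 | 5 (5/7 = 71.4%) | 2 | 1 | 6 |
| CDMS | 21 | 16 (16/21 = 76.2%) | 5 | 4 | 17 |
| OQ-45.2 (assumed) | 45 | 35 (35/45 = 77.8%) | 10 | 9 | 36 |
| CANSAS (assumed) | 20–25 | 15–19 | 5–6 | 4–5 | 16–20 |

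**Step 3: where one- or two-item scores can arise.** At k = 9, m = 7 (7/9 = 77.8%) leaves 2 items. At k = 10, 8/10 is not below 0.80, so m = 7 leaves 3. Only scales of nine items or fewer can therefore be scored from one or two items.

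**Step 4: illustration of the lost reliability.** If a fraction f of the items is answered and the full scale has reliability a, Spearman-Brown gives r = f·a / (1 + (f − 1)·a). The article reports no reliabilities, so a is assumed to lie between 0.80 and 0.90.
- CDIS, f = 2/7: a = 0.80 gives 0.229/0.429 = 0.53; a = 0.90 gives 0.257/0.357 = 0.72. With 6 of 7 items: 0.77 and 0.89.
- CDMS, f = 5/21: a = 0.80 gives 0.190/0.390 = 0.49; a = 0.90 gives 0.214/0.314 = 0.68. With 17 of 21 items: 0.76 and 0.88.

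These are worst cases for a single form, on the premise that each scale is one-dimensional. They are not an effect on any study estimate.

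**The case against.** The best defence is that this is a slip of wording. The authors probably meant at least 80% present, or less than 20% missing, and an experienced analyst would program that. This is plausible, but the article states no other limit, so the intention is inferred and the text still needs correcting.

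It can also be said that near-empty forms may be rare. Some data come from interviews by the study worker, and people too impaired to give meaningful answers are excluded. This stands: no item non-response rate is given, so the effect on the results cannot be sized. The reliabilities in the working are assumptions too, and would not apply directly if CDIS (involvement, satisfaction) or CDMS (preferences, autonomy, information seeking) were scored as subscales.

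A reader might infer that scores built on one or two items enter the analyses of needs, quality of life and symptoms. The article does not support that. Such scores are shown only for CDIS, and for CDRC only if its items are summed. On the assumed lengths, OQ-45.2 keeps at least 10 items and CANSAS 5 or 6. The length of the quality-of-life scale is not given. The link to outcomes at the two-item level runs through CDIS alone: it helps define the exposure, and satisfaction with decision making is itself a listed outcome.

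A reader might also infer bias, on the ground that people answer only the items that apply to them. Nothing in the article speaks to that.

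**Conclusion.** The rule is wrong as written. It permits scores from 2 of 7 CDIS items and 5 of 21 CDMS items, with 71% and 76% of items missing, and from 1 of 4 CDRC items if these are summed. Its grammar allows no stricter reading. Because the article chose to fix this threshold, it is not a detail left to an analysis plan.

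The consequence is added measurement error in the exposure and, to a degree set by scale length, in the outcomes. Its size in this study is unknown. The document shows neither bias nor any change in the primary result, and the sample size does not depend on this point. That the limit was meant for answered items is likely but needs the authors' confirmation.

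**What to change.** Once the authors have confirmed the intended limit, and before any scale is scored, replace the sentence with: *Sum scales will be prorated only when at least 80% of the items are answered (no more than 20% missing); otherwise the score is set to missing.* The boundary should be stated this exactly, because at least 80% answered and less than 20% missing differ at exactly 20%: a 45-item scale would allow 9 missing items under the first and 8 under the second.

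Then state separately what happens to the scores set to missing:
- **Outcome scores** can be left to the likelihood-based mixed model, which uses the remaining time points under a missing-at-random assumption.
- **Decision-making scores** cannot. A standard cluster analysis needs complete inputs, and a standard mixed model drops records with a missing covariate. They need their own handling, for example multiple imputation.

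The cost is one replaced sentence, one added sentence on missing decision-making scores, and some further missing scores. CDIS forms with 2 to 5 items missing, and CDMS forms with 5 to 16 missing, would no longer be scored. Design and sample size are unchanged.
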